**Supplement to the protocol, 2010**

At the start of the study, we performed our power calculations based on the fact that 44% of all primiparas at Aarhus University Hospital Skejby in 2007 had received epidural analgesia. We hypothesised that the observed frequency of epidural analgesia would be 25% in the intervention group, 35% in the placebo effect group, and 40 % in the placebo group.

According to these power calculations, we should include 328 participants in the hypnosis group, 328 participants in the active comparator group, and 152 participants in the control group to obtain a power of 80% (α 0.05 (two-sided)) to detect a difference of 5 percentage points (RR: 0.71) between the intervention and the active comparator groups. By including 152 participants in the control group, we would have a larger power to detect a difference of 15 percentage points (RR: 0.63) in the use of epidural analgesia between the intervention and the control groups.

Because we expected that some participants would develop medical conditions that required epidural analgesia during delivery, give birth prior to receiving their allocated intervention, or give birth by caesarean section, we decided to increase the sample size by 10% in all groups to a total of 890 participants.

In 2010, the study board experienced that in 2009 the general frequency of epidural analgesia in primiparas giving birth at Aarhus University Hospital Skejby had decreased to 34%.Therefore it was decided to adjust the sample size according to this new information.

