When the sample size was adjusted, we maintained the same sample ratios between the groups and hypothesised that the observed frequency of epidural analgesia would be 22 % in the intervention group, 30 % in the placebo effect group, and 32 % in the placebo group. To obtain a power of 80% (α 0.05 (two-sided)) in detecting a difference of 8 percentage points (RR: 0.73) between the intervention and the active comparator groups in the use of epidural analgesia and a difference of 10 percentage points (RR: 0.68) between the intervention and the control groups, we should include 446 participants in the hypnosis group, 446 participants in the active comparator group, and 226 participants in the control group, in total 1097 participants. Again, we further increased the sample size with an extra 10% to account for those women that would not be able to comply with their allocated treatment because of obstetric conditions, and reached a sample size of 1208.

**Appendix 1: Studies**  on hypnosis and childbirth

| **Study** | **Sample**  **N** | **Design** | **Intervention** | **Outcomes pain** |
| --- | --- | --- | --- | --- |
| Cyna et al  (2006) (24) | 77/3249  Australia | Case control  Self-selection | 3-4 x Individual sessions in self-hypnosis vs matched controls  Start: After 35 gw | Epidural analgesia |
| Cyna et al  (2004) (29) | 74/68 | Meta-analysis |  | Analgesic medication  RR 0,51 (95%CI; 0,28;0,95) |
| Mehl-Madonna  (2004) (34) | 250/250/(250)  USA | Randomised Controlled Trial  (a machted control group added in analysis) | Hypnosis vs Psychotherapy vs Paired control group  (vs matched control group)  Individual sessions  amount as needed, mean 3 times (Range 1- 60)  Start 1.or 2.trimester | In favor of hypnosis (HG/ PG/ PCG):  Any analgesic medication, (28%/67%/83%)  Epidural analgesia, (28%/67%/83%) |
| Martin et al  (2001) (36) | 22/20 | Randomised Controlled Trial | Hypnosis vs supportive counseling  Both groups 4 x  Hypnosis: Self-hypnosis Hypnoreflexlogymethod incl. information on labour and delivery  Start 20-24 gestational week | -Anaesthesia (45% vs 70%, NS)  -Pitocin (9% vs 30%, NS)  -Postpartum medication (9% vs 55%, NS) |
| Jenkins et al  (1993) (31) | 126/300  136/300 women  Wales | Case control | 6X ½ hour individual hypnosis vs matced controls | Analgesic medication |

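### The 2010 arm sizes (446, 446, 226) add to 1118, not the stated 1097, and do not keep the ratio said to be maintained; 226 is probably the control arm after the 10% increase

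*Protocol*

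**What the plan says.** The Supplement to the protocol, 2010, replaces the 2008 sample size after epidural use among primiparas at the hospital had fallen. It first repeats the earlier sizes: "328 participants in the hypnosis group, 328 participants in the active comparator group, and 152 participants in the control group". For the revision it says "we maintained the same sample ratios between the groups" and assumes epidural rates of "22 % in the intervention group, 30 % in the placebo effect group, and 32 % in the placebo group".

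It then gives the numbers needed for 80% power at a two-sided 0.05 level: "446 participants in the hypnosis group, 446 participants in the active comparator group, and 226 participants in the control group, in total 1097 participants". That power is claimed for two comparisons, hypnosis versus active comparator (8 percentage points) and "a difference of 10 percentage points (RR: 0.68) between the intervention and the control groups". Finally, 10% is added for women who cannot comply with their allocation for obstetric reasons, and the plan "reached a sample size of 1208". No breakdown of 1208 by arm is given.

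**The concern.** Three statements about the same set of numbers disagree: the arm sizes with their total, the arm sizes with the ratio, and the arm sizes with the final figure. This is the latest sample-size text in the protocol, so it sets the recruitment target for the primary endpoint.

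As printed, a reader cannot tell whether the final control arm is 226 or about 249 (226 × 1.1 = 248.6), or whether the study is to recruit 1208 women or about 1230. The same sentence carries the power claim for hypnosis versus control, which depends on how many controls were used in the calculation.

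**Working it through.** **Inputs, all from the 2010 supplement.** Earlier sizes 328, 328, 152. Revised sizes 446, 446, 226, with stated total 1097. Increase 10%. Final size 1208. Epidural rates 22% (hypnosis) and 32% (control). Two-sided alpha 0.05, power 80%.

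**1. Sum.** 446 + 446 + 226 = 1118, and 1118 − 1097 = 21. The stated total is not reproduced.

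**2. Ratio.** 328/152 = 2.16, but 446/226 = 1.97. Keeping the ratio would give 446 × 152/328 = 206.7 controls.

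**3. Final size.** 1118 × 1.1 = 1229.8, about 1230, not 1208. Dividing by 0.9 instead gives 1118/0.9 = 1242.2, which does not match either.

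**4. Which control size fits the other figures?** The stated total leaves 1097 − 2 × 446 = 205.

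| Controls before increase | Total before | Ratio | Arms after 10% (446 × 1.1 = 490.6, so 491) | Total after |
|---|---|---|---|---|
| 205 | 1097 | 2.18 | 491, 491, 226 (205 × 1.1 = 225.5) | 1208 |
| 206 | 1098 | 2.17 | 491, 491, 227 (206 × 1.1 = 226.6) | 1209 |
| 226 | 1118 | 1.97 | 491, 491, 249 (226 × 1.1 = 248.6) | 1231 |

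Only 205 reproduces both 1097 and 1208, and it keeps the ratio to within rounding (491/226 = 2.17). It also returns 226 as the inflated control arm. Applying 10% to the total alone gives 1097 × 1.1 = 1206.7, so rounding arm by arm explains 1208 better.

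**5. Power for 22% v 32%.** Normal approximation with pooled variance under the null:

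z = (|p1 − p2| − 1.96 × s0) / s1, and power = Φ(z), where s0 = √[p̄(1 − p̄)(1/n1 + 1/n2)], s1 = √[p1(1 − p1)/n1 + p2(1 − p2)/n2] and p̄ = (n1p1 + n2p2)/(n1 + n2).

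- 446 v 226: p̄ = 0.2536, s0 = 0.03553, s1 = 0.03671, z = 0.827, power 79.6%. This reproduces the stated 80%.
- 446 v 205: p̄ = 0.2515, s0 = 0.03661, s1 = 0.03803, z = 0.743, power 77.1%.
- 491 v 226: p̄ = 0.2515, s0 = 0.03488, s1 = 0.03623, z = 0.873, power 80.9%, if every enrolled woman is analysed.

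By this formula, 230 controls are the fewest that give 80% alongside 446 in the hypnosis arm.

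**The case against.** The strongest reply is that this is a clerical slip. If 226 is the control arm after the 10% increase, the final control target is right, 1208 is right, the ratio holds, and only one number stands in the wrong list. At 491 v 226 the control comparison has about 81% power, provided all enrolled women are analysed, so the planned comparison is not shown to be underpowered. Much of this stands, and it limits how far the point can go. A reader might infer that the control-arm target is wrong, or that it is overstated by some 20 women. The protocol does not support that, because 226 fits exactly as the inflated target.

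It can also be argued from power that 226 was meant before the increase, since 446 v 226 gives close to 80% and 446 v 205 gives 77.1%. This is a fair point but does not settle the matter. By the same formula, 446 per arm gives only 77.8% for the other comparison in that sentence (22% v 30%), so the stated 80% is not reproduced there either and is a weak guide to which control size was used.

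The reply does not remove the contradiction. The figures are in running prose, in current text, and nothing elsewhere in the protocol reconciles them. A sum of stated whole numbers has to be exact, even where the gap is only 1.9% (21/1097).

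**Conclusion.** The point holds as an internal contradiction in the operative sample size. The listed arms exceed their stated total by 21, depart from the ratio said to be kept, and lead to a final size about 22 above the one stated (1230 against 1208). These three facts need no assumption.

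That 226 is the inflated control figure, standing where 205 belongs, is the most likely explanation because it resolves all three conflicts at once. It remains an inference, since 1208 is not split by arm.

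The effect on power is modest. The figure for hypnosis versus control lies between about 77% and 81%, depending on which arm sizes are meant and on whether all enrolled women are analysed, which the supplement does not say. These values assume the stated rates and an uncorrected normal approximation. The finding concerns the stated target and its justification. It does not show that the trial is unsound or that the number of controls to be recruited is wrong.

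**What to change.** Rewrite the sentence so that it gives arm sizes before and after the 10% increase and both sets add up. The sponsor should check the original calculation and choose one of two forms:

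- If 226 is the inflated control arm: 446 / 446 / 205 = 1097 before and 491 / 491 / 226 = 1208 after. The ratio statement can stay. The uninflated control size should be given as 205, because 206 would give totals of 1098 and 1209 and introduce a new mismatch.
- If 226 is truly the size before the increase: restate the totals as 1118 and about 1230 (1231 if each arm is rounded separately), and delete the statement that the ratio was maintained.

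In either case, restate the power for hypnosis versus control for the arm size actually used, and say whether it refers to numbers before or after the increase.

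The first form costs one corrected sentence and no extra women. The second raises the target by about 22 women.

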**Aim**

The aim of the study is to investigate the effect of self-hypnosis during childbirth on the following endpoints:

Primary endpoint:

- The use of epidural analgesia during labour

Secondary endpoints:

- Duration of labour
- Birth progression at arrival at birth department
- Birth experience (pain, control, anxiety)
- Medical interventions during birth including mode of delivery
- Saliva cortisol profile at birth and 6 weeks post partum (p.p.)
- Infection during labour and the first 6 weeks p.p. (mother and child)
- Postnatal depression
- Breastfeeding duration
- Child's condition and wellbeing at birth and 6 months later
- Future mode of delivery

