**Power calculations**

The power calculations are based on the primary endpoint, use of epidural analgesia during childbirth. In 2007, 44% of all primiparas giving birth at Aarhus University Hospital Skejby received epidural analgesia. We presume that the women who want to take part in the project will have a lower frequency in the use of epidural analgesia, 40%, and that the use of epidural analgesia can be reduced to 35% by relaxation techniques, and 25% by self-hypnosis. On the basis of these assumptions, we must include 328 participants in the hypnosis group, 328 participants in the active comparator group, and 152 participants in the control group to obtain a power of 80% (α 0.05 (two-sided)) to detect a difference of 5 percentage points (RR: 0.71) between the intervention and the active comparator groups. By including 152 participants in the control group, we will have a larger power to detect a difference of 15 percentage points (RR: 0.63) in the use of epidural analgesia between the intervention and the control groups.

Because we expect that some participants will develop medical conditions that required epidural analgesia during delivery, give birth prior to receiving their allocated intervention, or give birth by caesarean section, we decide to increase the sample size by 10% in all groups to a total of 890 participants.

Using the estimated number of participants with regard to epidural blockade, a strength of 90% is needed to show a difference of 60 min in duration of labour of between the intervention and control groups. These calculations were performed based on an expected duration of labour of 480 min and 420 min in two groups of the same size, with a range of 220 min in both groups. On this basis, 283 participants will be included in each of these groups.

During the course of the study, an interim analysis will be undertaken after the first 12 months in order to make any necessary adjustments in number of participants

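### The 10% added for women unable to comply does not offset dilution if they are analysed as randomised, so 80% power at 1,208 holds only if the planned rates already include them

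*Protocol*

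**What the plan says.** The primary endpoint (Protocol, Aim) is "The use of epidural analgesia during labour". The secondary endpoints include "Medical interventions during birth including mode of delivery".

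The Supplement to the protocol, 2010 resets the assumed epidural rates to "22 % in the intervention group, 30 % in the placebo effect group, and 32 % in the placebo group". It gives the target as "To obtain a power of 80% (α 0.05 (two-sided)) in detecting a difference of 8 percentage points (RR: 0.73") and the base size as "446 participants in the hypnosis group, 446 participants in the active comparator group, and 226 participants in the control group, in total 1097 participants". It then "increased the sample size with an extra 10% to account for those women that would not be able to comply" with their allocated treatment for obstetric reasons, and arrives at 1,208.

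The section Power calculations says whom the 10% is for: women expected to "develop medical conditions that required epidural analgesia during delivery, give birth prior to receiving their allocated intervention, or give birth by caesarean section". The 2010 supplement repeats this list when it restates the 2008 calculation.

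The protocol does not say whether the 22/30/32% include these women, and it does not say that any of them will be left out of the analysis.

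**The concern.** Adding a percentage to the sample replaces observations that are lost. The women listed here are not lost. Table 1 of the protocol names medical records and the birth cohort as data sources at labour, so epidural use is known for all of them. For the first group on the list, it is close to being the endpoint event itself.

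If they stay in their allocated arm, as an analysis as randomised requires, the problem is not fewer observations but a smaller difference between arms. A factor of 1.10 is too small for that.

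The factor does roughly fit a plan in which a tenth of the women are removed (exact factor 1/0.9 = 1.111), so the wording could later be taken as permission to remove them. Two of the three reasons would then condition the primary comparison on the endpoint or on a birth outcome that arises after randomisation.

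At stake is how a null result would be read. A trial believed to have 80% power may have had several points less for the comparison that counts.

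**Working it through.** **Inputs from the protocol.** Two-sided α 0.05; 80% power; rates 22%, 30% and 32%; base 446/446/226; +10%; final size 1,208; and "we maintained the same sample ratios between the groups", which in 2008 were 328:328:152 (total 808).

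**Assumptions not in the protocol.** A share d of non-compliers, equal in all arms; no treatment effect among them; epidural rate q among them; planned rates that apply to compliers only.

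**Formula.** Power = Φ[(|p1-p2| - 1.96·s0)/s1], with s0 the pooled and s1 the unpooled standard error of the difference.

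**Step 1: the plan's own figures.**
- 2008, 25% v 35%, 328 per arm: 79.9%. The method reproduces the plan.
- 2010, 22% v 32%, 446 v 226: 79.6%. Reproduced.
- 2010, 22% v 30%, 446 per arm: s0 = √(2·0.26·0.74/446) = 0.02937, s1 = 0.02925, (0.08 - 1.96·0.02937)/0.02925 = 0.767, power 77.8%. Not reproduced: 80% needs 471 per arm (468 unpooled, 470 arcsine, 496 with continuity correction).
- Inflation: 1,097 × 1.10 = 1,206.7, close to 1,208. (446 + 446 + 226 is 1,118, not 1,097, a separate slip.)

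**Step 2: arm sizes at 1,208.** 1,208 × 328/808 = 490 and 1,208 × 152/808 = 227. With no dilution, power is 81.6% v active and 81.0% v control.

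**Step 3: dilution.** Each arm's rate becomes (1-d)·p + d·q, so the difference becomes (1-d)(p2-p1). With d = 0.10 and q = 0.30:
- Hypnosis: 0.9·0.22 + 0.03 = 22.8%
- Active: 0.9·0.30 + 0.03 = 30.0%
- Control: 0.9·0.32 + 0.03 = 31.8%

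Against active, the difference is 7.2 points, s0 = 0.02816, s1 = 0.02807, (0.072 - 1.96·0.02816)/0.02807 = 0.599, power 72.5%.

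| Assumption (490/490/227) | v active | v control |
|---|---|---|
| Planned rates already include these women | 81.6% | 81.0% |
| d = 10%, q = 0% | 75.9% | 75.5% |
| d = 10%, q = 30% | 72.5% | 72.1% |
| d = 10%, q = 50% | 70.6% | 70.2% |
| d = 10%, q = 100% | 66.7% | 66.4% |
| d = 1/11, q = 30% | 73.4% | – |
| d = 5%, q = 30% | 77.3% | 76.8% |
| d = 10%, q = 30%, half the effect survives (22.4% v 30.0%) | 77.3% | – |

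**Step 4: size needed.** The approximate factor is 1/(1-d)^2 = 1/0.81 = 1.235. Computed directly, 22.8% v 30.0% needs 588 per arm, or 2·588 + 588·152/328 ≈ 1,448 in all.

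**Step 5: separating the two causes.** Had the base been 471, +10% would give 518 per arm. Power is then 83.6% undiluted and 74.9% with d = 10%, q = 30%. Of the 7.5 points between 72.5% and 80%, about 2.4 come from the low base and about 5 from dilution.

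**Step 6: if 10% were removed instead.** 490 × 0.9 = 441 per arm, power 77.4%. The base of 446 already gives only 77.8%, so the allowance itself costs about 0.4 point.

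**The case against.** The strongest objection is that the planned rates may already include these women. The supplement speaks of the frequency expected to be observed in each group and starts from hospital figures for all primiparas (44% in 2007, 34% in 2009), with no exclusion for indication or caesarean. On that reading, applying dilution counts it twice, the 10% is a spare margin, and power v active is 81.6%. This stands as a possible reading. Against it, the supplement adds the 10% on top of the calculated size specifically for these women, which would then serve no purpose. The text does not settle the matter.

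Second, the protocol gives an inflation of 10%, not a non-compliance rate, and does not say that the training has no effect in these women. Table 1 starts the classes at weeks 34–36, so many women with a later caesarean or epidural indication would have attended. Only those who give birth first are plainly untreated. This also stands, and is why the 77% cases belong beside the 73%. The low end of the range is extreme too: q = 100% implies 37% in the active arm (0.27 + 0.10), above the 34% hospital rate.

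Third, a reader might infer that the protocol plans to drop these women and so bias the primary comparison. It does not say so. It only enlarges the sample, and the analysis set may be defined in a statistical analysis plan that is not at hand. The bias is conditional on a choice that this document does not make.

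**Conclusion.** The point holds in conditional form. If 22/30/32% are rates among compliers and these women are analysed as randomised with no effect among them, an extra 10% does not carry 80% power. At 10% non-compliance and a 30% epidural rate among them, power is about 73% v active and 72% v control, within about 67–76% over all possible epidural rates. A smaller share or a partly preserved effect brings it to about 77%. Dilution alone is enough for a shortfall, since a correct base would still give only about 75%.

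Two stronger statements are not supported. One is that the trial simply has 73% power: that figure rests on three inputs the protocol does not give, and all-comer rates would give 81.6%. The other is that removing the women would cost power because of the allowance: nearly all of the drop to 77% comes from the separate shortfall at 446 per arm.

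**What to change.** 1. State whether the 22%, 30% and 32% include the women for whom the 10% was added.
2. Replace the 80% claim with the power of the 1,208 design for the as-randomised comparison, giving the assumed share, the effect and epidural rate among these women, and the range: about 73% v active and 72% v control in the central case, 67–76% over the epidural rate, about 77% under milder dilution, and 81.6% v active if the rates are all-comer rates. Note that 446 per arm gives 77.8% for 22% v 30%.
3. Add a sentence that the 10% is a sample-size allowance and no ground for removing women because of an epidural indication, caesarean or non-attendance. Any such exclusion belongs only in an analysis labelled as sensitivity.

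The cost is wording and a less favourable stated power, with no extra women or data. Restoring 80% in the central case would instead take about 588 per arm in the two larger groups, roughly 1,450 in all. That is a decision for the sponsor and is not needed to correct the text.
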